**IRB Approved**

**06/24/13**

[figure not shown]

Logistic regression analysis will be used to analyze outcome data to determine the difference between the two regimens. With 40 patients enrolled in each arm, the study has 80% power to rule out a 15% difference in efficacy between the two regimens. This assumes a true response rate of 85% for both treatment groups.

For assessment of safety and tolerability, counts and percentages of patients with clinical or laboratory adverse experiences of the following type will be tabulated: (1) serious adverse experience; (2) drug-related adverse experiences that result in grade 3 or above laboratory toxicity; (3) drug related adverse experiences that lead to treatment interruption; (4) drug related adverse experiences leading to discontinuation.

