## 2. CORE PROTOCOL

### 2.1 OBJECTIVES AND HYPOTHESES

#### 2.1.1 Hypotheses

We hypothesize that the virologic efficacy (time to loss of virologic response) at 24 weeks will be at least as high following a regimen of Raltegravir + boosted Darunavir as with a regimen of Tenofovir + Emtricitabine + boosted Darunavir.

We further hypothesize that a regimen of Raltegravir + boosted Darunavir will not result in higher rates of adverse events at 24 weeks than a regimen of Tenofovir + Emtricitabine + boosted Darunavir.

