#### 2.1.2 Primary Objective

The primary objective is to determine whether a regimen of Raltegravir + Ritonavir-boosted Darunavir achieves a comparable virologic efficacy (TLOVR) at 24 weeks to Tenofovir + Emtricitabine + Ritonavir-boosted Darunavir

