## RADAR - Raltegravir And Darunavir Antiretroviral Regimen

- Time from randomization to virologic failure (HIV viral load of 1,000 copies/ml or greater at or after Week 16 and before Week 24, or two consecutive HIV viral load of 50 copies/ml or greater at or after Week 24)

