## 2.6 DATA ANALYSIS SUMMARY

The primary analysis of efficacy and safety will be based upon the All Patients As Treated (APaT) approach, which includes all patients who received one or more doses of the test drug therapy. All patients who take study medication will be included in the analysis of safety and tolerability. Only those adverse experiences that occur while on study therapy or within 14 days after discontinuation of study therapy will be included in the analysis.

This is an estimation study. The primary endpoint is the comparison of the efficacy of the test regimen (Raltegravir + Darunavir) to Tenofovir + Emtricitabine + Darunavir. The mean effects of the test regimen (Raltegravir + Darunavir) will be compared to comparator regimen.

The analysis will be time to loss of virologic response (TLOVR) [12]. This analysis defines responders as subjects maintaining a minimum of two sequential HIV viral load <50 through the scheduled visits without intervening replicated rebounds or treatment discontinuations.

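### The named primary analysis, logistic regression for a difference, does not match the stated aim of ruling out a 15-point deficit or the listed time-to-failure outcome

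*Protocol*

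**What the plan says.** - **Aim.** Section 2.1.1 hypothesises that "virologic efficacy (time to loss of virologic response) at 24 weeks will be at least as high" on the raltegravir regimen. The primary objective in Section 2.1.2 asks whether that regimen "achieves a comparable virologic efficacy (TLOVR) at 24 weeks". Comparable is not defined numerically.
- **Size.** Sections 2.6 and 3.4 say: "With 40 patients enrolled in each arm, the study has 80% power to rule out a 15% difference in efficacy between the two regimens". Both assume a true response of 85% in each arm.
- **Analysis.** The same two sections say: "Logistic regression analysis will be used to analyze outcome data to determine the difference between the two regimens". They also speak of comparing mean effects.
- **Primary variable.** Section 2.4 (Study Endpoints) lists "Time from randomization to virologic failure". Sections 2.6 and 3.4 instead describe a TLOVR analysis: "This analysis defines responders as subjects maintaining a minimum of two sequential HIV viral load <50", with no replicated rebound or treatment discontinuation in between.
- **Framework.** Section 2.6 says "This is an estimation study", and Section 1.4 calls it a pilot. No significance level, interval or confidence level is given.

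**The concern.** Two mismatches are written into the protocol.

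**Question and scale.** A test for a difference asks whether the data contradict equality. The aim asks whether they contradict a deficit of 15 points or more. In a small trial the data may contradict neither, so a non-significant test does not show that 15 points is excluded. The usual logistic output is an odds ratio, and the odds ratio that corresponds to 15 points changes with the control rate.

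**Variable.** A time to failure and a responder status are different outcomes. Logistic regression uses neither event time nor censoring, and the protocol names no survival method for the Section 2.4 outcome. The definitions also differ in content: treatment discontinuation ends TLOVR response, whereas the Section 2.4 outcome is defined by viral load alone.

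At stake is the conclusion the trial exists to support. A clearly worse regimen could be described as comparable because a small trial found no significant difference.

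**Working it through.** **Inputs.** From Sections 2.6 and 3.4: 40 per arm, 85% response in both arms, 15% (read as percentage points), 80% power. From Section 1.4: 80 patients, 1:1. Alpha and sidedness are not stated, so they are assumed below. No dropout is assumed.

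**1. The protocol's own figure.** SE = sqrt(2 × 0.85 × 0.15 / 40) = 0.0798. Power to exclude a 15-point deficit = Φ(0.15/0.0798 − z) = Φ(1.879 − z), where z is the one-sided critical value.

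| One-sided alpha | Power |
|---|---|
| 0.025 | 46.8% |
| 0.05 | 59.2% |
| 0.10 | 72.5% |
| 0.15 | 80.0% |

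The stated 80% is reached only at a one-sided alpha of about 0.15. That is a separate defect, but it bears on the cost of the fix.

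**2. The odds ratio equal to a 15-point deficit.** For control rate p, OR = [(p − 0.15)/(1.15 − p)] / [p/(1 − p)].

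| Control rate | OR |
|---|---|
| 80% | 0.46 |
| 85% | 0.41 |
| 90% | 0.33 |
| 95% | 0.21 |

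No single odds ratio stands for 15 points.

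**3. A true 15-point deficit.** Exact enumeration over Bin(40, 0.70) for the test arm and Bin(40, 0.85) for control:

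| Result | Probability |
|---|---|
| Two-sided 5% test not significant, likelihood ratio | 0.63 |
| Same, Pearson chi-square | 1 − 0.366 = 0.63 |
| Same, Wald log-odds | 1 − 0.344 = 0.66 |
| Lower 95% limit of the difference above −15 points, Newcombe | 0.028 |
| Same, Wald | 0.028 |

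**4. One data set.** Take 28/40 versus 34/40. OR = (28/12)/(34/6) = 0.41. The log odds ratio is −0.887 with SE sqrt(1/28 + 1/12 + 1/34 + 1/6) = 0.561, so p is about 0.11. The difference is −15 points, with Wald 95% CI −33.0 to +3.0. The test finds no difference, while the interval leaves open a deficit of more than twice 15 points.

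**5. What an interval rule costs.** With 85% in both arms, exact enumeration puts the chance that the lower 95% limit clears −15 points at 0.45 (Newcombe) or 0.50 (Wald). Identical results of 34/40 and 34/40 give a lower limit of −16.2 (Newcombe) or −15.6 (Wald) and do not clear it.

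**The case against.** - **Logistic regression fits the responder.** This stands. Sections 2.6 and 3.4 define a binary status, the sample size uses a response rate, and Table 2 counts outcome categories. A reader might infer that the model suits no outcome in the protocol. The text does not support that. The fault is the unreconciled conflict with the Section 2.4 outcome.
- **Logistic regression can address 15 points.** This also stands. The model can give a standardised risk difference with a confidence interval. A reader might infer that the method is inherently unable to rule out 15 points. It is not, but the protocol does not specify that output.
- **The protocol never says a non-significant odds ratio means comparable.** Correct. It calls the trial an estimation study, and ruling out 15% is the language of a confidence limit. The 63-66% therefore belongs to a reading that the text permits, not to a rule that it states.
- **Interval method, level and weighting are matters for the SAP.** In large part yes, and their absence alone would be no finding. What remains is in the protocol itself: the method it names answers a different question from the one its hypothesis and sizing sentence pose, and it gives two different primary variables.
- **An interval rule would turn a pilot into a pass/fail test.** A fair caution. The fix therefore keeps the estimate and interval as the primary result and uses −15 points only to govern what may be claimed.

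**Conclusion.** The point holds in this form: the named analysis does not match the aim, and the listed primary outcome does not match the variable analysed. The consequence is conditional. If non-significance were taken as comparability, about 63-66% of trials with a true 70% versus 85% response would miss the deficit, whereas a 95% lower-limit rule would wrongly exclude 15 points in about 3%. These figures assume 40 evaluable patients per arm, a two-sided 5% test, no dropout, and 15% meaning percentage points. Only the sample size and the 85% come directly from the protocol. A reader might go further and conclude that the trial will rest comparability on a non-significant odds ratio. The protocol states no such rule, so that conclusion is not supported. The matter should be corrected, and needs no change to the trial's conduct.

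**What to change.** 1. Name one primary variable: week-24 TLOVR responder status.
2. Make the primary result the difference in week-24 response proportions (raltegravir arm minus tenofovir/emtricitabine arm) with a two-sided 95% confidence interval. Newcombe or Miettinen-Nurminen would serve. So would a standardised risk difference from the logistic model, adjusted for the baseline viral-load and CD4 strata in Section 2.4.
3. State that a 15-point deficit is ruled out only if the lower limit is above −15 points. Otherwise report the estimate and interval without claiming comparability. Never infer comparability from a non-significant odds ratio.
4. Keep the odds ratio as supportive, and use Kaplan-Meier for the Section 2.4 time-to-failure outcome.
5. Remove the wording on mean effects.

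The cost is revised wording in Sections 2.4, 2.6 and 3.4 and a few lines of code, with no new data. The downside should be disclosed. With 40 per arm and 85% in both arms, the lower limit clears −15 points only about 45% (Newcombe) to 50% (Wald) of the time, so the trial will often end as an estimate with its interval. That agrees with its description as a pilot estimation study.

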### **3.2.3.3 Allocation**

Eighty (80) patients meeting the eligibility requirements will be randomized on a 1:1 basis to one of the two treatment groups:

1. Group A: will receive Raltegravir + Ritonavir-boosted Darunavir
2. Group B: will receive Tenofovir + Emtricitabine + Ritonavir-boosted Darunavir

Patients will be provided with medications according to their treatment groups and will be instructed to take them as previously described. The patients will also be instructed on the procedure for reporting of adverse experiences.

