**IRB Approved**

**06/24/13**

[figure not shown]

Logistic regression analysis will be used to analyze outcome data to determine the difference between the two regimens. With 40 patients enrolled in each arm, the study has 80% power to rule out a 15% difference in efficacy between the two regimens. This assumes a true response rate of 85% for both treatment groups.

The reasons for failure at week 48 should be the primary reason for the earliest treatment failure. For any visit, subjects who have achieved confirmed virologic success (two consecutive visits with HIV viral load < 50 copies/mL) will be considered successes. All others should be classified into the other appropriate categories listed in Table 2. All events occurring in the window should be considered events for that visit.

All patients who take study medication will be included in the analysis of safety and tolerability. Only those adverse experiences that occur while on study therapy, or within 14 days after discontinuation of study therapy will be included in the analysis.

For assessment of safety and tolerability, counts and percentages of patients with clinical or laboratory adverse experiences of the following type will be tabulated (1) serious adverse experience, (2) drug-related adverse experiences that result in grade 3 or above laboratory toxicity; (3) drug related adverse experiences that lead to treatment interruption; (4) drug related adverse experiences leading to discontinuation.

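### The stated 80% power to rule out a 15-point difference with 40 per arm is not reproduced at any conventional confidence level, and the protocol states no level

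*Protocol*

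**What the plan says.** Sections 2.6 and 3.4 of the protocol carry the same claim: "With 40 patients enrolled in each arm, the study has 80% power to rule out a 15% difference in efficacy between the two regimens". The sentence after it supplies the remaining input: "This assumes a true response rate of 85% for both treatment groups". Section 3.2.3.3 confirms 80 patients and 1:1 allocation. No type I error rate, sidedness or confidence level accompanies the claim in either place.

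The aim is worded in two ways. Section 2.1.1 hypothesises that efficacy "will be at least as high following a regimen of Raltegravir + boosted Darunavir as with a regimen of Tenofovir + Emtricitabine + boosted Darunavir", and Section 2.1.2 asks whether the test regimen "achieves a comparable virologic efficacy (TLOVR) at 24 weeks". Both are non-inferiority wording. Section 1.4, on the other hand, calls the trial a pilot, and Section 2.6 says "This is an estimation study".

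**The concern.** Sample size, margin and response rate are all printed, so the power can be recomputed once an error rate is chosen. Forty per arm looks small for excluding 15 points when response is 85%: the margin is less than two standard errors of the difference, whereas 80% power at one-sided 2.5% needs about 2.8.

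The power sentence is the only quantitative justification for 80 patients. If it is wrong, an ethics board, a funder or a reader of the results has been given too high a chance that the trial can answer its primary question when the two regimens are truly equal.

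**Working it through.** **Inputs from the protocol (Sections 2.6 and 3.4):** n = 40 per arm; true response 0.85 in both arms, so the true difference is 0; difference to be ruled out 0.15, read as absolute percentage points; stated power 80%.

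**Assumed, because the protocol is silent:** a one-sided bound, following the non-inferiority wording of Section 2.1.1, at 2.5% (95% CI) or 5% (90% CI). Wider levels are shown for completeness.

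**Standard error.** SE = √(2 × 0.85 × 0.15 / 40) = 0.0798, and 0.15 / SE = 1.879.

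**Attempt to reproduce 80%.** Power = Φ(1.879 − z₁₋α):

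| One-sided alpha | CI level | Power | n per arm for 80% |
|---|---|---|---|
| 0.025 | 95% | Φ(1.879 − 1.960) = 46.8% | 89 |
| 0.05 | 90% | Φ(1.879 − 1.645) = 59.2% | 71 |
| 0.10 | 80% | 72.5% | 52 |
| 0.15 | 70% | 80.0% | 40 |

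Solving for the alpha that yields 80%: 1 − Φ(1.879 − 0.842) = 0.150.

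Sample size check: n = 2 × 0.1275 × (1.960 + 0.842)² / 0.0225 = 89 per arm. With 1.645 in place of 1.960 it is 70.07, rounded up to 71.

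**Is the normal approximation to blame?** No. Exact binomial enumeration gives:

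| Method | One-sided 2.5% | One-sided 5% |
|---|---|---|
| Wald | 49.6% | 59.9% |
| Newcombe | 45.3% | 59.3% |
| Farrington-Manning | 43.7% | 57.1% |

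**Does another reading give 80%?**

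| Reading | Power |
|---|---|
| Variance under the null (85% vs 70%) | 35% at 2.5%, 49% at 5% |
| Logit scale | 29% at 2.5%, 41% at 5% |
| Log-hazard, 12 expected events (80 × 0.15) | 27% at 2.5%, 39% at 5% |
| Two-sided equivalence, 5% per side | 18% |
| Superiority, 85% vs 70% | 36% (two-sided 5%), 48% (one-sided 5%) |
| 80 per arm instead of 80 in total | 76% at 2.5%, 84% at 5% |
| Superiority, 85% vs about 100% | 73% (two-sided 5%), 83% (one-sided 5%) |

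The last two come nearest, but the first of them contradicts 40 per arm and the second contradicts equal 85% response in both groups.

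**Margin available with 80% power at 40 per arm.** (1.960 + 0.842) × 0.0798 = 22.4 points (95% CI); (1.645 + 0.842) × 0.0798 = 19.9 points (90% CI).

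**Precision at the planning value, 34/40 in each arm.** The 95% CI half-width is 1.960 × 0.0798 = 15.6 points (Wald) or 16.2 (Newcombe), so 15 is not excluded. The 90% CI half-width is 1.645 × 0.0798 = 13.1 points (Wald) or 13.5 (Newcombe), so 15 is excluded.

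**Sensitivity to the response rate.** At 90% in both arms, SE = √(2 × 0.90 × 0.10 / 40) = 0.0671 and power is 61% (95% CI) or 72% (90% CI). At 95% it is 87% or 92%. The protocol plans on 85%, and Section 3.1 cites 84% at 48 weeks for darunavir/ritonavir with tenofovir/emtricitabine in treatment-naïve patients.

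**The case against.** **No confidence level is given, so 80% is not strictly contradicted.** This stands in part. The 47% and 59% do not follow from the protocol's inputs alone; they need an assumed level. A level may also be set in an analysis plan that is not at hand, so its absence is not the finding. But a power figure printed without an error rate will be read at a conventional one, and at one-sided 2.5%, 5% and even 10% it is too high. Nothing in the protocol suggests that a 70% CI was meant; if it was, the sentence has to say so.

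**This is a pilot estimation study with no formal non-inferiority decision rule.** That is true, and it limits the consequence: no conclusion is tied to excluding 15 points. It does not make the figure correct, and the protocol itself chose to claim that it can "rule out a 15% difference in efficacy between the two regimens".

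**Stronger readings that the documents do not support.** A reader might infer that the design cannot exclude a 15-point deficit even when the arms are observed to be identical. That holds only for a 95% CI near 34/40 per arm. The 90% CI at 34/40 excludes 15, and so does the 95% CI at 36/40 (half-width 13.1 points by Wald, 14.4 by Newcombe). At 35/40 the 95% result depends on the method (14.5 by Wald, 15.3 by Newcombe). A reader might also infer that an inconclusive result is the likely outcome for a truly equal regimen. With a 95% CI it is close to an even chance, and with a 90% CI exclusion is the more likely outcome at 59%. How readers would interpret a failure to exclude 15 points is conjecture.

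**Conclusion.** The power statement is wrong as written at any conventional confidence level. Against the stated 80%, power is about 47% with a 95% CI or 59% with a 90% CI, a shortfall of roughly 33 or 21 percentage points. The printed figure needs a one-sided alpha of about 0.15.

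This rests on the protocol's 40 per arm, 85% response in both arms and a 15-point absolute margin, and on two assumptions made here: a one-sided bound and a conventional level. The choice of method does not rescue the claim, because exact methods and the other readings compatible with the stated inputs give similar or lower power.

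The error lies in the stated justification for the sample size. It does not show that 80 patients is an unacceptable size for a pilot, nor that the trial cannot give useful estimates.

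**What to change.** Keep 80 patients. Replace the power sentence in Sections 2.6 and 3.4 with:

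> With 40 per arm and 85% response in both arms, the expected 95% CI half-width for the difference is about 16 points (90% CI: about 13). Power to exclude a 15-point deficit is about 47% (95% CI) or 59% (90% CI). 80% power is available for a margin of about 22 points (95% CI) or 20 points (90% CI).

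State which confidence level applies, and use the same wording in both sections. If a 70% CI really was intended, declare it.

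The change is to wording only: no extra patients, and no change to conduct or analysis. The cost is that the stated power becomes less favourable.

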### 3. PROTOCOL DETAILS

#### 3.1 RATIONALE

HAART regimens with the most experience in demonstrating virologic and immunologic efficacy – and therefore recommended by the DHHS for initial therapy of antiretroviral naïve patients – are those composed of 2 NRTI and 1 NNRTI or a boosted PI. Apart from limited data on PI monotherapy [1, 2], and switch studies [3], NRTI-free regimens have never been used on a significant number of patients for a significant amount of time. Such regimens have usually been found to have significantly lower virologic efficacy [1]. However, because of concerns about long-term drug toxicity, the development of drug resistance, and potential complications in pregnant women, it is imperative that other drug combinations, including NRTI-free regimens, be investigated as possible alternative initial regimens.

NRTI use is associated with significant toxicity, including mitochondrial dysfunction (mostly attributed to thymidine-analogue NRTIs): lipoatrophy, peripheral neuropathy, pancreatitis, and lactic acidosis [4]. There's also the risk of hypersensitivity reaction from Abacavir, and caution is needed when using Tenofovir in patients with renal failure. Recent data (including ACTG trials 5110, 5125s, and 5142) suggest that a switch to NRTI-free regimens might significantly improve the side-effect profile [3, 5]. NRTI-free arms had lower rates of lipoatrophy, but also higher rates of hypertriglyceridemia and a trend towards higher virologic failure rate [5]. The NRTI-free regimens in all these studies were Lopinavir with an NNRTI (Efavirenz or Nevirapine), and it's reasonable to expect that the use of a PI with a better metabolic profile than LPV/r might significantly improve the side-effect profile of such regimens.

A suggestion from these and other trial results is that NRTIs might be associated with other than the known complications, but these have been difficult to detect because there have been few long-term comparisons of NRTI-containing and NRTI-free regimens, and very few have been done on naïve HIV-infected patients [6]. Finding effective NRTI-free regimens would have a number of potential benefits including: 1) a significant expansion of therapeutic options; despite the growing number of antiretrovirals, treatment options might still be significantly limited in a patient with a number of baseline NRTI mutations [7] or poor NRTI tolerance; 2) potential avoidance of toxicities;

Raltegravir is a leading candidate in a new class of antiretroviral medications called integrase inhibitors. Inhibition of integrase prevents insertion of HIV DNA into the human

**IRB Approved**

**06/24/13**

[figure not shown]

DNA genome, thus blocking the ability of HIV to replicate. It is administered orally every twelve hours and does not require boosting with low-dose ritonavir to achieve therapeutic concentrations. Raltegravir is not a potent inhibitor or inducer of cytochrome P (CYP) 3A4, and it is predominantly metabolized by glucuronidation, specifically by the enzyme UDP-glucuronosyltransferase (UGT) 1A1.

Raltegravir has been shown to have excellent virologic efficacy in naïve and heavily treatment experienced patients. It also has been shown to have unusually rapid virologic response [8]. This profile might be excellent in delaying emergence of viral resistance in naïve patients.

A two-part, Phase II, dose-ranging trial in treatment-naïve patients compared 10-day Raltegravir monotherapy in 28 patients with placebo in seven patients.

Thirty-five patients were enrolled (6–8 patients per treatment group) and completed 10 days of therapy; the mean baseline log10 HIV RNA level ranged from 4.5 to 5.0 copies/mL in each group. On day 10, the mean decrease from baseline in the log10 HIV RNA level was 20.2 copies/mL for the placebo group and 21.9, 22.0, 21.7 and 22.2 log10 copies/mL for the MK-0518 100-, 200-, 400-, and 600-mg treatment groups, respectively. All dose groups had superior antiretroviral activity compared with placebo (P, 0.001 for comparison of each dose with placebo). At least 50% of patients in each MK-0518 dose group achieved an HIV RNA level ,400 [8, 9]. In the second part of the study, 198 treatment-naïve patients (including the initial 30 patients) were randomly assigned to receive either the same twice-daily dosages of Raltegravir or efavirenz 600 mg once daily, both in combination with tenofovir and lamivudine. After 24 weeks of therapy, 85% to 95% of patients on Raltegravir-based regimens achieved viral loads of less than 50 copies/ml across all dosages. In the efavirenz-based regimen, 92% of patients achieved viral loads less than 50 copies/ml. However, viral load reduction was achieved more quickly with Raltegravir regimens.[7]

Three phase III trials of Raltegravir in treatment experienced patients have been conducted (BENCHMRK trials).[10, 11] In both of these studies, more than 75 percent of patients receiving Raltegravir plus optimized background therapy (OBT) achieved viral load (HIV RNA) reductions to less than 400 copies/mL compared to more than 40 percent of patients receiving placebo plus OBT (BENCHMRK-1, 77 percent of patients (N=232) receiving Raltegravir plus OBT vs. 41 percent of patients (N=118) receiving placebo plus OBT; and BENCHMRK-2, 77 percent of patients (N=230) receiving Raltegravir plus OBT vs. 43 percent of patients (N=119) receiving placebo plus OBT, p<0.001 for both studies respectively). Both studies also showed that after 16 weeks of treatment, Raltegravir plus OBT was generally well tolerated. In addition, there were few discontinuations due to adverse experiences (BENCHMRK-1, four patients receiving Raltegravir plus OBT and four patients receiving placebo plus OBT; for BENCHMRK-2, five patients receiving Raltegravir plus OBT and one patient receiving placebo plus OBT).

In subgroup analysis of the BENCHMRK trials, use of Raltegravir and Darunavir was associated with 90% virologic responses (HIV RNA < 400 copies/mL) at 24 weeks in treatment experienced subjects.

Raltegravir is primarily metabolized by the liver via glucuronidation and is neither an inducer nor an inhibitor of CYP3A4. This should clearly reduce potential drug

